### 11.2 Statistical and Analytical Plans

A Statistical Analysis plan will be written for the study.

### 11.3 Summary of Variables

Continuous variables (e.g., age) will be summarised using descriptive statistics (number of observations, mean, median, minimum, maximum and standard deviation). Categorical

variables (such as gender) will be summarised using frequency tables (presenting the number and percentage). All summary tables will clearly indicate the number of subjects included in the summary.

## **11.4 Data Sets to be Analysed**

### **11.4.1 Safety Analysis Set**

The safety analysis set comprises all subjects who have received treatment and for whom at least one item of safety data is available. Documentation that the subject did not experience any adverse events constitutes safety information.

### **11.4.2 Full Analysis Set**

The full analysis set (FAS) comprises all subjects who provided consent and were enrolled in the study.

#### **Intent to Treat Set**

The intent to treat (ITT) set comprises all subjects in the FAS who received treatment and for whom at least one item of efficacy data is available.

### **11.4.3 Per-Protocol Set**

No per protocol set will be defined.

## **11.5 Summary of Subject Disposition**

The number and percentage of subjects in each analysis set will be summarised. In addition, the number (and percentage) of subjects completing the study will be presented. For subjects not completing the study the reason for premature withdrawal will be summarised.

## **11.6 Baseline and Background Characteristics**

All baseline characteristics (demography, medical history) will be summarised using descriptive statistics (mean, median, standard deviation, minimum and maximum) for continuous variables and frequency tables (frequency and percentage) for categorical variables.

## **11.7 Efficacy Analyses**

### **Primary efficacy endpoint: Complete Remission (CR)**

The number of lesions treated per subject will be summarised.

The number (and percentage) of lesions in each category (CR, partial response [PR], stable disease [SD] and progressive disease [PD]) at each timepoint, and the overall best response will be presented. The percentage of lesions achieving CR during the study (i.e., CR is the

best overall response) will be estimated and presented with exact 95% confidence limits overall and by tumour type.

### **Secondary efficacy endpoints: Change from baseline in QoL, comfort of treatment, and cosmetic outcomes**

The QoL questionnaire will be scored according to the author's instructions. Change from baseline in score will be calculated. Descriptive statistics will be presented for actual score and change from baseline by timepoint, overall and by tumour type (BCC/SCC). A mixed model will be fitted with change from baseline as the outcome variable. Baseline score will be included as a covariate and timepoint (6 months/12 months) tumour type, tumour stage as factors. Other relevant prognostic factors assessed at baseline will be included. Subject will be included as a repeated term to acknowledge the data structure. From the model the adjusted mean change at each timepoint will be obtained and presented with 95% confidence limits. Adjusted mean change will be estimated overall and by tumour type.

Comfort with treatment is being assessed using a short questionnaire. The frequency (and percentage) of subjects reporting each option for each question will be presented.

Cosmetic outcome (subject and clinician) is being assessed at two timepoints (12 months and 24 months respectively) using a Visual Analogue Scale (VAS). Descriptive statistics will be presented overall and by tumour type (BCC or SCC). A mixed model will be fitted with VAS as the outcome variable. Tumour type and tumour stage will be included as factors. Other relevant prognostic factors assessed at Baseline will be included. From the model the adjusted mean score will be obtained and presented with 95% confidence limits. Adjusted mean score will be estimated overall and by tumour type.

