### **Appendix 3: VAS Cosmetic outcome (clinician and subject rated)**

On a scale of 0-10 (0 being very poor and 10 being no visible wound) what is the cosmetic outcome of the Rhenium-SCT treated lesion(s)?

[figure not shown]

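### The cosmetic-outcome model names no visit term and promises one adjusted mean, so read literally the endpoint averages 12 and 24 months; the scoring unit is also unclear

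*Protocol*

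**What the plan says.** Section 11.7 introduces the measure with "Cosmetic outcome (subject and clinician) is being assessed at two timepoints (12 months and 24 months respectively) using a Visual Analogue Scale (VAS"). The analysis is then "A mixed model will be fitted with VAS as the outcome variable. Tumour type and tumour stage will be included as factors", with other baseline prognostic factors to be added but not named. The output is one quantity: "From the model the adjusted mean score will be obtained and presented with 95% confidence limits", overall and by tumour type. The efficacy analysis in the synopsis describes the model in the same way, and the endpoint in Section 5.4 attaches no visit to the mean.

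The quality-of-life model in the same section is fuller. Its terms are "Baseline score will be included as a covariate and timepoint (6 months/12 months) tumour type, tumour stage as factors". It adds "Subject will be included as a repeated term to acknowledge the data structure" and reports per visit: "From the model the adjusted mean change at each timepoint will be obtained and presented with 95% confidence limits".

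Other places that bear on the point:

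- Table 2 and the 12- and 24-month visit lists in Section 9.1.3 have both raters scoring at both visits.
- The synopsis evaluation criteria (efficacy item 5) give 12 months as the only time of cosmetic assessment.
- Appendix 3 asks, on a 0-10 scale, "what is the cosmetic outcome of the Rhenium-SCT treated lesion(s"). Section 7.1 allows up to three target lesions per subject, and Sections 5.4 and 11.9 require results by tumour type.

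**The concern.** A mean taken over a score collected at two visits, from a model with no visit term, is a mean over both visits. It then answers neither how the skin looks at 12 months nor how it looks at 24 months, and its value depends on how many subjects return for the later visit. Section 11.11 uses all available data without imputation. Sections 6.1, 9.1.4 and 9.2.1 have subjects leave on progression or further treatment of the lesion, so the mixture is set partly by who stays.

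The second part concerns the unit of the score. Tumour type and stage belong to a lesion, whereas the Appendix 3 question can be read as one score for everything treated. If it is one score, a subject with both a BCC and an SCC has no defined place in the by-type means. If it is one score per lesion, the protocol does not say so and names no within-subject clustering for this model. A later analysis plan cannot recover lesion scores that the App and eCRF did not collect.

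At stake is the meaning of one named secondary endpoint. The primary endpoint is untouched.

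**Working it through.** The protocol gives no VAS standard deviation, no 12-24 month correlation and no expected return rate at 24 months, so it has no figure of its own to reproduce here. The values of *f*, *rho* and the simulation settings below are assumptions.

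**1. The two models in Section 11.7 side by side**

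| | Quality of life | Cosmetic VAS |
|---|---|---|
| Visits analysed | 6, 12 months | 12, 24 months |
| Visit as a factor | yes | not named |
| Subject term | repeated term | not named |
| Reported mean | at each timepoint | one, no timepoint |

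The wording "is being assessed at two timepoints (12 months and 24 months respectively") could suggest one rater per visit. Table 2 and Section 9.1.3 rule that out. No place says whether the two raters are modelled separately.

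**2. What the single mean averages**

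Let *f* be the share of subjects scored at 12 months who are also scored at 24 months. With every score counted equally, the weight of 24 months is *f*/(1 + *f*).

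| *f* (assumed) | weight at 12 months | weight at 24 months |
|---|---|---|
| 1.0 | 50% | 50% |
| 0.9 | 1/1.9 = 53% | 47% |
| 0.8 | 1/1.8 = 56% | 44% |
| 0.7 | 1/1.7 = 59% | 41% |

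If the true 24-month mean lay 1 point above the 12-month mean (assumed), the reported value would sit 0.50 point above the 12-month mean at full return and 0.41 point above it at 70% return.

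A random subject effect does not remove the mixing. It gives 24 months the weight [*f*/(1 + *rho*)] / [2*f*/(1 + *rho*) + 1 - *f*]. At *f* = 0.7 and *rho* = 0.5 this is 0.467/(0.933 + 0.3) = 38%, against 41% above.

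**3. Interval width**

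With two scores per subject and correlation *rho*, the correct standard error is sqrt(1 + *rho*) times the one that assumes independence. The independence version is therefore too small by 1 - 1/sqrt(1 + *rho*), and its nominal 95% interval covers 2*Phi*(1.96/sqrt(1 + *rho*)) - 1.

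- *rho* = 0.5: 1 - 1/1.225 = 18% too small; coverage 89.0%.
- *rho* = 0.7: 1 - 1/1.304 = 23% too small; coverage 86.7%.

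These figures apply only if no subject term is fitted. A simulation (120 subjects, SD 2, visit difference 1 point, 150 replicates) compared the reported standard error of a random-subject model without visit with the spread of its estimates:

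| *rho* | return at 24 months | reported SE | spread of estimates |
|---|---|---|---|
| 0.5 | 100% | 0.158 | 0.152 |
| 0.7 | 100% | 0.168 | 0.171 |
| 0.5 | 80% | 0.163 | 0.174 |
| 0.7 | 80% | 0.172 | 0.164 |

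The spread carries a simulation error of about 1/sqrt(2 x 150) = 6%, so these agree. With a subject term the interval is about right even when visit is left out; the mean is still a mixture.

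**The case against.** The strongest reply is that this is abbreviation, with detail to follow in the analysis plan that Section 11.2 announces.

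For the subject term that reply stands. A reader might infer from the contrast with quality of life that repeated cosmetic scores will be treated as independent and the interval will be too narrow. The text does not support this. It calls the analysis a mixed model, which needs some random or repeated effect. The synopsis also describes the quality-of-life model without a subject term, although Section 11.7 shows that it has one. Silence on that term is therefore weak evidence that it is left out.

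For visit the reply is weaker. Both the synopsis and Section 11.7 name timepoint for quality of life and omit it for cosmesis, and the endpoint definitions carry the same contrast. The 12-month item in the synopsis criteria suggests a main timepoint, but it disagrees with the two-visit description elsewhere, so it needs reconciling and does not settle the question.

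A reader might also infer that a subject with a BCC and an SCC has only one VAS. Appendix 3 does not establish that, since its wording does not exclude a score per lesion. The unit is ambiguous, and the share of mixed-type subjects is not given, so no effect on the by-type means can be computed.

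On dropout, Section 11.1 expects a complete response rate near 100%, so planned loss through progression is small. Means per visit would not by themselves cure selective loss at 24 months. Finally, no hypothesis test, threshold or decision hangs on this endpoint.

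**Conclusion.** The point holds for the visit term. As written, the adjusted cosmetic mean has no timepoint and, taken literally, is an attendance-weighted average of 12 and 24 months: 50/50 at full return and 59/41 at an assumed 70% return. This differs from the quality-of-life model beside it and conflicts with the 12-month criterion in the synopsis. How far the value moves depends on the change between visits, which is not given.

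The scoring unit is a real ambiguity that should be settled before data are collected. It is not a demonstrated error.

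A too narrow interval is not established. It would follow only if the subject term were actually left out, and the protocol does not say that it is.

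The change is worth making because a named secondary endpoint lacks a defined timepoint and the model correction is free.

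**What to change.** 1. In Section 11.7 and the synopsis, add visit (12/24 months) as a factor in the cosmetic model and state subject as the repeated or random term, as for quality of life.
2. State that subject-rated and clinician-rated VAS are modelled separately.
3. Report the adjusted mean at each visit, with 12 months as the main one, and word the endpoint in Section 5.4 and the synopsis to match.
4. Reconcile efficacy item 5 of the synopsis criteria with the two-visit schedule.
5. Record the 0-10 score for each target lesion, so that type and stage attach to the lesion scored, and model lesions as clustered within subject.

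Items 1 to 4 are wording only and need no new data. Item 5 changes the App and eCRF and adds up to two items per rater per visit for subjects with more than one lesion.

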## **11.8 Safety Analyses**

### **11.8.1.1 Adverse Events**

Adverse events will be coded using MedDRA and comprehensively summarised by System Organ Class (SOC) and Preferred Term (PT) overall, by severity and by relationship to Rhenium-SCT.

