### **5.5 Safety Endpoint**

- Safety: Adverse events (AEs) by severity and by relationship to Rhenium-SCT, including radiation dermatitis, skin ulceration, alopecia, skin induration, hypo/hyperpigmentation, and telangiectasia.

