## **6. STUDY DESIGN**

### **6.1 Overall Study Design**

This is a prospective, multicentre, single arm, open-label, phase IV/ Post Marketing Clinical Follow-up (PMCF), study consisting of:

- A screening period of up to 30 days duration, to ensure that the subject is eligible for the study
- A follow-up period of 24 months. Each subject will remain in the study for 24 months from the time of their treatment with Rhenium-SCT. Subjects requiring further or alternative treatments for the target lesions during the trial period, will leave the study.

The study is completed with the last visit of last subject.

Details on all study visits can be found in the time and events schedule in Section 9.

An interim analysis is planned once 50% of subjects have recorded a 6-month follow-up visit.

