| Histology if lesion visible/suspected/or per clinical practice |                     |                                     |                                       |                                        |                                                                          |                                        |                            |                            | X                                                     | X                      |

|                                                            |  |  |  |  |  |  |  |  |  |   |
|------------------------------------------------------------|--|--|--|--|--|--|--|--|--|---|
| Review for wound complications or radiation changes |  |  |  |  |  |  |  |  |  | X |
|------------------------------------------------------------|--|--|--|--|--|--|--|--|--|---|

\*QoL, subject rated cosmetic outcome, monthly photos obtained through subject trial App; \*\* baseline visual RECIST is to measure lesions only; \*\*\* AE's to be recorded for the first 30 days post treatment. After this only treatment related AEs are to be recorded: \*\*\*\* Histology must be confirmed to meet the inclusion criteria before any baseline assessments are conducted

AE: Adverse events; QoL: Quality of life; RECIST: Response evaluation criteria in solid tumours

NOTE: In case of early termination: In case of premature termination during the follow-up period, the investigator shall endeavour to arrange a premature end of study visit and perform examinations according to end of treatment visit. If the subject does not enter the follow-up period, this is the study termination (end of study) visit.

NOTE: Radiation changes at months 24 are to be recorded as the CTCAE grading in protocol appendix 1, excluding Radiation dermatitis.

NOTE: Subjects who do not have a smart phone will complete QoL questionnaire, Comfort of treatment questionnaire and Cosmetic outcome on paper questionnaires at the follow up visits. Monthly photos are not taken for subjects without a smart phone, instead photos are taken at the site, at follow-up visits only.

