### **9.1.2.3 Day 30 Phone call**

On day 30, post treatment, the site will call the subject as this forms the end of the AE reported period. After this time, only AEs deemed related to treatment will be collected. During the call any AEs are to be recorded into the eCRF.

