## 10. PHARMACOVIGILANCE

### 10.1 Definition of Adverse Events

An AE is defined as any untoward medical occurrence in a subject administered a treatment and which does not necessarily have a causal relationship with this treatment. An AE can therefore be any new sign, symptom, illness, or syndrome, any abnormal laboratory values, if judged clinically significant in the opinion of the investigator, any worsening (change in nature, severity or frequency) of a concomitant or pre-existing illness, any adverse effect of the investigational medicinal product/device, including comparator or concomitant medication, any product/device interactions, any adverse effect of an invasive procedure required by the protocol or any accident or injury, whether or not related to the investigational medicinal product/device.

All AEs fall into one of two categories: “non-serious” and “serious”.

In this study, the following medical events will not be considered to fall under the definition of an AE:

- Surgical procedures or other therapeutic interventions themselves are not AEs, but the condition for which the surgery/intervention is required is an AE and should be documented accordingly.
- Planned surgical measures and the condition(s) leading to these measures are not AEs, if the condition(s) was (were) known before the period of observation and did not worsen during study. In the latter case, the condition should be reported as medical history.
- Any SAEs detected by the investigator in a study subject after the end of the period of observation, which the investigator does not consider to be related to prior study treatment or procedures

Progression of the cancer under study is not considered an AE unless it results in hospitalization or death.

The study will collect all AEs for the first 30 days of the study, after which only AE's deemed treatment (device) related will be collected.

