## 10.4 Period of Observation

All AEs that occur after the consent form is signed but before treatment with investigational medicinal products/devices must be reported by the investigator if they cause the subject to be excluded from the study or are the result of a protocol-specified intervention.

For the purposes of this study, the period of observation for collection of AEs extends from the time when the subject signed informed consent until 30 days after the treatment administration.

If the Investigator detects a SAE in a study subject after the end of the period of observation (i.e., 30 days post treatment to 24 months) and considers the event related to prior study treatment or procedures, he or she should contact the Medical Monitor to determine how the AE should be documented and reported. An SAE form should be completed and sent to Medical Monitor.

Association of an event with the device can be excluded (at investigator discretion if deemed unrelated to treatment) if the event occurs later than the following latency period after the last product/device application:

- 30 days for non-serious adverse events,
- 30 days for SAEs
- 30 days for pregnancy, or 30 days if the subject initiates new anticancer therapy, whichever is earlier

If events occur after these latency periods, they will not be recorded, unless deemed associated (related) with the device treatment.

Any SAE brought to the attention of an investigator at any time outside of the time period specified above must be reported immediately to the Sponsor if the event is considered to be product/device related.

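### The AE summaries in 11.8.1.1 state no time window, although events of any relationship are collected to day 30 and only related events after that

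*Protocol*

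**What the plan says.** The safety endpoint in Protocol section 5.5 is "Adverse events (AEs) by severity and by relationship to Rhenium-SCT", with a list of skin toxicities and no time window. The analysis in 11.8.1.1 follows it: events are to be "comprehensively summarised by System Organ Class (SOC) and Preferred Term (PT) overall, by severity and by relationship to Rhenium-SCT". Section 11.4.1 defines a single safety analysis set. Neither section divides the study at day 30, defines a treatment-emergent period or adjusts for observation time.

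Collection changes at day 30:

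- Section 10.1 collects "all AEs for the first 30 days of the study, after which only AE's deemed treatment (device) related will be collected".
- The footnote to Table 2 reads "AE's to be recorded for the first 30 days post treatment. After this only treatment related AEs are to be recorded".
- Section 9.1.2.3, on the day 30 call, reads "After this time, only AEs deemed related to treatment will be collected".
- Section 10.4 says of later events: "If events occur after these latency periods, they will not be recorded, unless deemed associated (related) with the device treatment".

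Follow-up is much longer. Section 6.1 states "Each subject will remain in the study for 24 months from the time of their treatment with Rhenium-SCT". That is a maximum, because section 9.1.4 has subjects leave on progression or when they need further treatment.

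Serious AEs have two rules. Section 10.4 gives 30 days. Section 10.6 requires serious AEs of any relationship to be reported for 90 days, or 30 days if new anticancer therapy starts.

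**The concern.** After day 30, the judged relationship of a non-serious event decides whether it enters the database at all. A whole-study table by relationship is therefore partly fixed by the collection rule, since its unrelated rows can fill for about a month and its related rows for up to two years. The overall row and the severity totals add these two unequal periods together. They are neither a 30-day nor a 24-month frequency, and a reader cannot tell which is meant.

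Late related events are expected here. The synopsis calls for CTCAE grading of acute and late effects, grading visits run to month 24, and the endpoint names induration, pigmentation change and telangiectasia. Section 10.5.4 also assigns events whose relatedness cannot be assessed to the possible category. Section 11.8.3 says no other safety assessments are performed, so 11.8.1.1 is the only safety analysis the protocol specifies.

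**Working it through.** The protocol states no AE rate, total or related share, so there is no figure of its own to reproduce.

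**Step 1: windows, from the documents.**

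- Related AEs: up to 24 months = 24 × 365.25/12 = 730.5 days.
- Unrelated non-serious AEs: 30 days after treatment.
- Ratio: 730.5/30 = 24.35. Unrelated events are observable for 30/730.5 = 4.1% of maximum follow-up.
- Serious AEs under section 10.6: 730.5/90 = 8.1. Under section 10.4 the ratio is again 24.35.

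**Step 2: effect on a table, with assumed rates.** Take 100 subjects, all followed for 24 months. Let u be unrelated AEs per subject-month, a related AEs per subject in the first 30 days, and l late related AEs per subject-month. Thirty days is m = 30/(365.25/12) = 0.986 months. With u = 0.05, a = 0.3 and l = 0.01, all assumed:

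- unrelated to day 30: 100 × u × m = 4.9
- unrelated to month 24 (not collected): 100 × u × 24 = 120
- related to day 30: 100 × a = 30
- related after day 30: 100 × l × (24 − m) = 100 × 0.01 × 23.01 = 23.0

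| Table | Related | Unrelated | Total | Related share |
|---|---|---|---|---|
| Day 0 to 30, all AEs | 30 | 4.9 | 34.9 | 85.9% |
| Pooled, no window | 53.0 | 4.9 | 57.9 | 91.5% |
| Full 24-month capture (not available) | 53.0 | 120 | 173.0 | 30.6% |

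The pooled total matches neither of the other two. The related count of 53.0 is the same in the last two rows, so pooling does not alter the 24-month incidence of related AEs.

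**Step 3: sensitivity.** With a = 0.3, u from 0.02 to 0.10 and l from 0 to 0.03:

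- related share to day 30: 75.3% to 93.8%
- pooled share: 75.3% to 98.0%
- share under full 24-month capture: 11.1% to 67.4%

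With l = 0 the pooled and 30-day tables are identical. The largest shift from pooling alone is at u = 0.10 and l = 0.03, from 75.3% to 90.9%, or 15.6 points.

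**Step 4: what causes which gap.** The step from 85.9% to 91.5% comes from pooling, and separate tables remove it. The gap from either figure to 30.6% arises because unrelated AEs after day 30 are never recorded. No re-tabulation closes that gap.

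**The case against.** **This is detail for the statistical analysis plan (SAP).** Section 11.8.1.1 is one sentence, section 11.2 promises an SAP, and the sentence is compatible with tables split at day 30. That is fair: an SAP not shown may already make the split, and absent table shells are no fault. What stands is that the protocol fixes a collection rule that changes at day 30, and then states an endpoint and an analysis that take no account of the change.

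**The protocol does have an AE window.** Section 10.4 ends the period of observation 30 days after treatment, and section 10.1 takes later unrelated serious events out of the AE definition. But related events continue to be collected, and 11.8.1.1 does not say whether its tables stop at day 30. If they do, late related events have no table. If they do not, the windows are mixed.

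**The device-safety result is intact.** This stands for related AEs over 24 months. The named skin toxicities are also CTCAE-graded at scheduled visits, with dermatitis excluded at month 24, and that grading does not depend on relatedness. Nor does the protocol define a related share; a reader would derive one from the table.

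**The collection rule, not the tabulation, causes most of the apparent distortion.** This also stands. A reader might infer that tabulation alone turns a small true related share into a very large one. Steps 2 to 4 of the working do not support that: the large gap follows from what is not collected.

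**Conclusion.** The point holds as a defect of specification. Tables that follow 11.8.1.1 literally would give overall and severity totals, and a related-versus-unrelated comparison, built from windows differing about 24-fold (about 8-fold for serious AEs if the 90-day rule applies). These ratios follow from the protocol and take 24 months as the maximum follow-up.

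The effect on reported percentages cannot be derived from the documents. Under the assumed rates pooling moves the related share by 0 to 15.6 points, and by 5.6 points in the base case (85.9% to 91.5%).

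Two stronger readings go too far. One is that all safety results are distorted: the 24-month incidence of related AEs is not. The other is that every unrelated event disappears after day 30: section 10.6, as written, still requires unrelated serious AEs to be reported to day 90, in conflict with section 10.4.

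**What to change.** In section 11.8, replace the single undated summary with three, each labelled with its window:

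- **A.** All AEs from the start of AE collection to day 30, overall, by severity and by relationship. Starting at collection rather than at Day 0 keeps the pre-treatment events that section 10.4 makes reportable.
- **B.** Treatment-related AEs from Day 0 to month 24, by severity, split by onset up to day 30 and after it.
- **C.** Serious AEs and deaths of any relationship, over the serious-AE reporting window. Sections 10.4 and 10.6 must first be reconciled on that window. Without this table, unrelated serious events between days 31 and 90 would be reportable but have no place in the output.

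State that no all-AE total and no related share will be computed across windows. The report should also say that unrelated non-serious AEs after day 30 were not collected, since this cannot be recovered at analysis.

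The cost is one paragraph and one or two extra table shells. No new data are needed.
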